**Protocol Revision History**

Initial Approval 01/30/13

Amendment #1 07/26/13

Amendment #2 05/13/14

Amendment #3 08/27/14

# SCHEMA

Patients with brain metastases elected for

Gamma-knife (GK) alone without

whole brain radiation therapy (WBRT)

Standard GK (with MRI + perfusion MR)

1 week (7-10 days) after GK: MRI + perfusion MR

Routine follow-up with standard MRI every 3 months

# BACKGROUND

Brain metastases occur in 20% to 40% of patients with cancer (1). Traditionally, whole brain radiation therapy (WBRT) has been the standard treatment approach (2). More recently, stereotactic radiosurgery (SRS) has gained popularity in treating those with limited brain metastases (3, 4). SRS is a technique that employs multiple convergent beams of radiation to provide a large, highly conformal dose to a selected target. It is typically delivered using a Cobalt-60-based device (also known as Gamma-Knife (GK)) or a linear accelerator (4). The Siteman Cancer Center at Washington University serves as a major regional referral center for GK and treats over 100 patients with brain metastasis per year.

Recent randomized studies have demonstrated equivalence in survival between those treated with SRS alone versus SRS and WBRT (5, 6). Addition of WBRT was associated with significant decline in learning and memory recall at 4 months after treatment (7). However, omission of WBRT was associated with increased risk of local recurrence as well as elsewhere-brain failure (5-7). The one-year local tumor recurrence rate after SRS alone ranged around 27-33% in the three randomized studies, as contrasted to 0-19% after SRS and WBRT (5-7). Currently, selection between SRS alone versus SRS plus WBRT for treatment of limited brain metastases is controversial (4).

Accurate and non-invasive imaging that can provide early prediction of treatment response to SRS would provide the much needed guidance for the treatment selection. For those with poor response to SRS, additional WBRT may be added to prevent tumor recurrence. This adaptive approach would promote individualized therapy to increase the therapeutic ratio. Furthermore, novel radiotherapy technique such as hippocampal-sparing intensity-modulated WBRT may allow increased dose to the resistant lesions while reducing the neuro-cognitive effect of WBRT by decreasing the dose to the hippocampus (8, 9). However, before the adaptive approach can be incorporated in routine clinical practice, the most crucial first step is to identify an accurate and non-invasive imaging method for early treatment response monitoring.

Advancements in magnetic resonance imaging (MRI) techniques have allowed for non-invasive assessment of physiological changes. Notably, dynamic susceptibility-weighted contrast-enhanced perfusion MRI (DSC-PMR) is a promising imaging technique that may be used as a biomarker for treatment response monitoring. DSC-PMR exploits signal changes that accompany the passage of a gadolinium-based contrast agent through the cerebrovascular system. It measures hemodynamic changes that reflect the underlying microvasculature and angiogenesis (10). Different measurement parameters of DSC-PMR have been shown to correlate with tumor microvasculature density, capillary blood volume, and microvasculature leakage (11-13). Since tumor microvasculature is an important component of the microenvironment that promotes brain tumor progression and treatment resistance (14, 15), its changes after treatment may reflect tumor response.

## Preliminary Studies of Dynamic PET for Early Response Monitoring

Using small animal imaging, we have previously shown that dynamic positron emission tomography (PET) may provide informative assessment of early radiation necrosis and radiation change of tumor xenografts after a single dose of radiotherapy (16). Detailed comparison of PET changes with corresponding histological changes also suggests that the optimal timing to differentiate the radioresistant versus radiosensitive region would be 7 days after a single-fraction of high-dose radiotherapy, with 30 days being the next optimal time point (16). Follow-up studies have shown that PET parameters that measure perfusion changes during the first week of fractionated radiotherapy might be predictive of tumor control. Although PET is not routinely used to measure perfusion changes in brain tumors, the principles demonstrated by the animal studies are thought provoking.

## Correlative Studies of DSC-PMR

Three clinical studies of DSC-PMR have suggested that perfusion changes during or shortly after radiotherapy may correlate to tumor response. In a prospective study of 23 glioma patients treated with conformal radiotherapy, Cao *et al.* conducted DSC-PMR at Weeks 1 and 3 during the radiotherapy. They found that fractional changes of cerebral blood volume (CBV) on DSC-PMR were predictive for survival (17). In another retrospective study of 36 glioma patients treated with radiotherapy and temozolomide, Mangla *et al.* reported that increased magnitude of relative CBV from DSC-PMR at one month after treatment was associated with significantly worse survival (18). The third study performed DSC-PMR on 18 patients with brain metastases at 6 weeks and at 3 months after SRS. The study showed that high regional CBV value at 6 weeks after SRS was predictive of tumor recurrence, with a sensitivity of 91% and a specificity of 71% (19). However, this study only performed DSC-PMR at 6 weeks after SRS and did not image tumors during the first two weeks after SRS.

## Significance

Although there is no direct therapeutic benefit to the participant for participating in this study, the study offers promising potential benefit to society, with important clinical implication on the management of brain metastases. If DSC-PMR can accurately assess for early treatment response after GK as hypothesized, hippocampal-sparing intensity-modulated WBRT may be selectively used to decrease local tumor recurrence for high risk patients while avoiding unnecessary irradiation for low risk patients. This would have an important implication as we continue to push for personalized medicine in cancer treatment. We would expect that the data generated from this pilot study will lead to larger grant to fund studies to incorporate DSC-PMR for a phase II study for incorporating hippocampal-sparing intensity-modulated WBRT after SRS to provide individualized radiation therapy for patients with brain metastases. Furthermore, the additional MRI at Weeks 1 and 4 may provide indirect benefit to the participants by allow early detection of new brain metastases, intracranial bleeding or stroke.

## Interim Analysis

During our interim analysis after enrollment of 11 patients, we determined that compliance for the Week 4 scan has been very poor. It is unlikely that any meaningful data will be obtained by having any additional patients complete the Week 4 scan. The study objectives have been revised to clarify that the analysis of the Week 1 scan is the primary objective and that the analysis of Week 4 scan is the secondary objective. After the approval of this amendment, the Week 4 scan will not be obtained for the remaining patients.

# OBJECTIVES

## Primary Aim

To evaluate and compare changes of tumor perfusion on DSC-PMR occurring between at Week 1 after GK versus at baseline (before GK) as a predictor for time to local tumor progression. Specific quantitative values of relative cerebral blood volume (rCBV), relative cerebral blood flow (rCBF), relative peak height (rPH), and percentage of signal-intensity recovery (PSR) will be determined from each DSC-PMR. The changes of these parameters will be correlated with local control after GK to identify their predictive accuracy.

# PATIENT ELIGIBILITY

## Inclusion Criteria

1. Patient must have newly diagnosed brain metastases visible on brain MRI. A biopsy of the lesion is not required as long as the patient has a biopsy-proven malignancy elsewhere and a clinician deems the lesion to be metastatic.
2. At least one brain metastasis must be ≥ 1cm to allow adequate quantitative imaging measurement for DSC-PMR.
3. Patient must be clinically eligible for and elect to be treated with GK alone without WBRT.
4. Patient must be ≥ 18 years of age.
5. Patient must have Karnofsky Performance Status (KPS) of at least 60 (see Appendix A).
6. Patient may be part of other clinical trials (as long as no other local treatments beyond GK such as WBRT or other local therapy are indicated to the brain) or imaging studies.
7. Patient or legally authorized representative must be able to understand and willing to sign a written informed consent document.

## Exclusion Criteria

1. Patient must not have any medical contraindications to MRI (e.g., unsafe foreign metallic implants, incompatible pacemaker, inability to lie still for long periods, severe to end-stage kidney disease or on hemodialysis).
2. Patient must not be pregnant or breastfeeding.
3. Patient must not have an estimated glomerular filtration rate (eGFR) < 60 mL/min/1.73m^2^.
4. Patient must not have melanoma.
5. Patient must not have hemorrhagic lesions.

# PATIENT REGISTRATION

Patients must not start any protocol intervention prior to registration through the Siteman Cancer Center. Patients may be consented and registered either before or after Gamma Knife surgery.

The following steps must be taken before registering patients to this study:

1. Confirmation of patient eligibility
2. Registration of the patient in the Siteman Cancer Center database
3. Assignment of unique patient number (UPN)

## Confirmation of Patient Eligibility

Confirmation of patient eligibility includes the information listed below:

1. Registering coordinator’s name and contact information
2. Registering MD’s name
3. Patient’s race, sex, and DOB
4. Copy of signed consent form
5. Completed eligibility checklist, signed and dated by a member of the study team
6. Copy of appropriate source documentation confirming patient eligibility

## Patient Registration in the Siteman Cancer Center Database

Patients must be registered through the Siteman Cancer Center database.

## Assignment of UPN

Each patient will be identified with a unique patient number (UPN) for this study. Patients will also be identified by first, middle, and last initials. If the patient has no middle initial, a dash will be used on the case report forms (CRFs). All data will be recorded with this identification number on the appropriate CRFs.

# METHODS

## Pre-Scan Data Collection

Data from a standard of care pre-treatment H&P (including KPS) and pre-treatment MRI of the brain will be collected in the CRFs.

Data from the standard radiosurgery treatment for brain metastasis will be collected in the CRFs, including number and location of lesions treated. As per routine care, patients will undergo standard MRI and CT for tumor localization and treatment planning. Data from this imaging will be collected in the CRFs as well. Prior to GK, patients must have undergone DSC-PMR as part of one pre-treatment scan. DSC-PMR is routinely included in the standard MRI on the day of GK as part of our routine clinical practice. If it has been performed as part of the standard pre-treatment MRI, it is not required at the time of GK. All pre-treatment procedures and evaluations, and treatment with GK itself, is part of routine care and is not dictated by this protocol; data from these evaluations will be collected in the case report forms as part of the on-study data.

## MRI and DSC-PMR

Additional MRIs with DSC-PMR will be performed at Week 1 (range: 7-10 days) after GK. Given that this additional MRI scan is not routine clinical practice, it will be performed at 3 Tesla combined PET-MRI scanner in the Center for Clinical Imaging Research (CCIR) for logistic reasons. The MRI component of the CCIR PET-MRI scanner is identical to the 3 Tesla clinical MRI scanner; PET imaging will not be utilized during this study. In the event the CCIR PET-MRI scanner is down, then clinical MRI scanner will be used. The standard FDA-approved head coil will be used. DSC-PMR will be performed with tracer method in which gadolinium contrast agents is injected and subsequent T2*-weighted gradient echo-planar images are acquired as the contrast passes through the brain. The DSC-PMR scanning time is approximately 3-5 minutes. The MRI scan at Weeks 1 will also include standard sequences such as T1 with and without contrast, so the total scanning time will be 30 minutes.

All participants scheduled to undergo gadolinium contrast enhanced MRI will be evaluated for potential renal insufficiency by calculation of an estimated glomerular filtration rate (eGFR) using the standard calculator provided by the NIH/National Kidney Disease Education Program (found at <http://www.nkdep.nih.gov/professionals/gfr_calculators/orig_con.htm>).  Plasma creatinine (mg/dL) shall be obtained from the medical record, or if none is available from the medical record within the last 90 days, it will be obtained on the day of scanning, prior to MRI.  If the contrast is administered for clinical purposes, the standard Barnes Jewish Hospital/Mallinckrodt Institute of Radiology algorithm for contrast dosing shall be used.  Contrast shall not be administered for research purposes in participants with an eGFR < 60 mL/min/1.73m^2^.

## Data Management

Clinical MR images will be sent to the Clinical Desktop system and will have standard clinical interpretations provided by the Department of Radiology. The investigational MRI imaging at Week 1 after GK will be reviewed by [name] (co-principal investigator) and reported in the Clinical Desktop system. This represents potential benefit to the patients, as incidental findings of new brain metastases, intracranial bleeding, or stroke may be detected early. For clinical sequences, post-processing will be performed according to standard protocols. In addition, research and clinical MR data without identifying patient information will be archived on the Central Neuroimaging Data Archive (CNDA) to allow for long-term follow up.

## Processing of DSC-PMR

All MRI data will undergo coregistration and will be resampled into atlas space for viewing and processing. DSC-PMR will be processed to obtain rCBV, rCBF, rPH, PSR for each region of interest (22), see Appendix C. Regions of interest (ROI) will be generated based upon the clinical T1-post contrast and FLAIR images. ROI will include the enhancing tumor volume, the non-enhancing area of T2 hyperintensity surrounding the enhancing tumor, and a matching ROI from normal brain in the contralateral hemisphere. Given the DSC-PMR data will not be used in clinical care, the parameters in Appendix C may be completed in batch up to 6 months from the completion of radiosurgery.

## Follow-Up

Standard clinical follow up will occur every 3 months from the date of GK for at least 12 months as per standard of care. Standard MRI imaging is routinely done prior to each follow-up visit. Of note, at Week 1 after GK, protocol patients will only have the MRI with DSC-PMR without a clinical visit. Specific information regarding local tumor recurrence, complete response, elsewhere-brain failure, clinical deterioration (in the form of KPS score), radiation necrosis, and overall survival should be assessed at each visit and will be audited by research coordinators periodically. Follow-up beyond this time will not be tracked for this study and will be at the discretion of the treating physician.

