# DATA SUBMISSION SCHEDULE

| **Case Report Form** | **Time point** |
| --- | --- |
| Consent Form | At time of consent |
| Eligibility Checklist  Registration  On-Study Form | At time of registration |
| GK Form | At time of GK |
| DSC-PMR Form | Baseline/screening or at time of GK (or both)  1 week after GK  [*The DSC-PMR parameters in Appendix C May be completed up to 6 months from the time of radiosurgery] |
| Adverse Events Form | AE information will be collected during the 8-hour period following each research DSC-PMR scan |
| Follow-Up Form | 3 months after GK  6 months after GK  9 months after GK  12 months after GK |

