# STATISTICAL CONSIDERATIONS

## Sample Size

This is a nonrandomized imaging study with a pre-specified sample size of 20 patients. Different metastatic lesions treated with radiosurgery will be analyzed independently. Based on institutional experience, the average number of lesions is estimated at 3 per patient giving us a sample size of approximately 60 for the primary endpoint of local control.

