## Study Endpoint

The primary endpoint of the study is time to local progression of each treated and evaluable brain metastasis. Secondary endpoints will include radiation necrosis, complete response, elsewhere-brain failure, and clinical deterioration.

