## Definition of Clinical Outcomes

Local tumor recurrence versus radiation necrosis can be a difficult diagnostic dilemma. The gold standard for this diagnosis will be based upon pathological diagnosis, when available. We would recommend any suspicious lesion be investigated and biopsied. If biopsy is not possible, the patient will be followed clinically and radiographically. Cases where clinical and radiographic findings demonstrate progressive disease, as defined by the MacDonald criteria (20), will be considered as recurrent tumor. Radiation necrosis will be defined by pathology, when available. When no pathology is available, we will use the final clinical diagnosis based on clinical course and management. Complete response is defined as no residue enhancing lesion on MRI. Elsewhere brain failure is defined as appearance of brain metastases outside of prior GK region, which can be diagnosed radiographically and does not require pathological confirmation. Clinical deterioration will be assessed based on the KPS scale (Appendix A).

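### Outcome tracking ends at 12 months, so an equivocal, unbiopsied lesion on the 12-month MRI has no recorded follow-up by which to separate recurrence from radiation necrosis

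*Protocol*

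**What the plan says.** The primary endpoint in section 10.2 is defined per lesion: "The primary endpoint of the study is time to local progression of each treated and evaluable brain metastasis". Radiation necrosis is a secondary endpoint.

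Section 5.5 sets the observation schedule: "Standard clinical follow up will occur every 3 months from the date of GK for at least 12 months as per standard of care". It then closes the window: "Follow-up beyond this time will not be tracked for this study and will be at the discretion of the treating physician". The words *at least* might suggest that later data could be used, but the form schedule in section 7 settles the matter. Its follow-up forms are due at "3 months after GK 6 months after GK 9 months after GK 12 months after GK", and none is listed after that.

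Section 10.3 makes pathology the reference standard when it exists. Otherwise, "If biopsy is not possible, the patient will be followed clinically and radiographically", with no duration given. Two rules then apply without pathology: findings that show progression by the MacDonald criteria count as recurrence, and necrosis is assigned from the final clinical diagnosis, which rests on course and management. Section 5.6 leaves biopsy or resection to the treating physician.

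The Appendix B form has columns for complete response, local failure and radiation necrosis, plus a comments field. A column is left blank when its event has not occurred. There is no entry for an undetermined lesion.

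**The concern.** The outcome definition needs information that arises after the first suspicious scan, and the collection window closes at the last scheduled scan. A lesion first suspicious at month 3 can have three further scheduled MRIs inside the window (months 6, 9 and 12). One first suspicious at month 12 has none. Ascertainment is therefore weakest for lesions detected last.

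An equivocal lesion at month 12 must be marked on incomplete evidence or left blank. If it is marked as local failure, some necrosis may enter the primary endpoint as events. If it is left blank, it looks in the form's table exactly like a controlled lesion unless someone uses the comments field. With about 16-20 events expected at best, one or two wrong labels could visibly move a Cox or ROC estimate of the perfusion parameters.

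The collection window is fixed in the protocol. An analysis plan can say how undetermined lesions are coded or censored, but it cannot recover a classification that was never collected.

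**Working it through.** **Inputs**

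- Patients: 20, from section 10.1 ("This is a nonrandomized imaging study with a pre-specified sample size of 20 patients").
- Lesions: "the average number of lesions is estimated at 3 per patient giving us a sample size of approximately 60" (section 10.1).
- One-year local recurrence, p: section 1 states "The one-year local tumor recurrence rate after SRS alone ranged around 27-33% in the three randomized studies". This is a background figure, not a stated design assumption.
- MRI every 3 months, last tracked at month 12: sections 5.5 and 7.
- Not given, so assumed below: the shape of the hazard, the death rate, and the share of late suspicious lesions that stay equivocal.

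**Step 1: the plan's own figure.** 20 × 3 = 60 lesions, which reproduces. The protocol states no event count, alpha or power to check.

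**Step 2: expected events by 12 months, no deaths.** 60 × 0.27 = 16.2 and 60 × 0.33 = 19.8.

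**Step 3: share first seen on the 12-month MRI.** With constant hazard, S(12) = 1 − p and S(9) = (1 − p)^0.75. Events arising between months 9 and 12 are first seen at month 12, so the share is [S(9) − S(12)] / p.

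| p | S(9) | S(9) − S(12) | Share of events | Lesions (× 60) |
|---|---|---|---|---|
| 0.27 | 0.790 | 0.060 | 22.1% | 3.6 |
| 0.30 | 0.765 | 0.065 | 21.8% | 3.9 |
| 0.33 | 0.741 | 0.071 | 21.4% | 4.2 |

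**Step 4: competing death (assumed median survival 6-18 months).** Let h = −ln(1 − p)/12, d = ln 2/median and F(x) = [h/(h + d)] × [1 − exp(−(h + d)x)]. The share is [F(12) − F(9)] / F(12).

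- p = 0.27, median 6 months: 9.1 events, share 11.8%, 1.1 lesions.
- p = 0.27, median 18 months: 13.1 events, share 18.2%, 2.4 lesions.
- p = 0.33, median 6 months: 11.2 events, share 11.3%, 1.3 lesions.
- p = 0.33, median 18 months: 16.1 events, share 17.6%, 2.8 lesions.

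The range is 11-18%, or about 1.1-2.8 lesions.

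**Step 5: hazard not constant (assumed Weibull, no deaths).** With cumulative hazard H = −ln(1 − p) at month 12, S(9) = exp(−H × 0.75^k).

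- Shape k = 0.5 (early failures): share 11-12%.
- Shape k = 2 (late failures): share 39-40%.

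**Step 6: from first seen to unresolved.** Steps 3-5 count lesions first seen at month 12. The share left unresolved is that share times the fraction u that cannot be classified at the visit. Using step 3:

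- u = 0.25: 0.25 × 21.4% to 0.25 × 22.1% = 5.3-5.5% of events, about 1 lesion.
- u = 0.50: 0.50 × 21.4% to 0.50 × 22.1% = 10.7-11.1%, about 1.8-2.1 lesions.
- u = 1: 21.4-22.1%, the ceiling under the step 3 assumptions.

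The protocol does not give u. Lesions that are truly necrosis and first appear in the same window would add to the unresolved count; no rate is given for these either.

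**The case against.** The strongest reply is that section 10.3 already has a working rule. Progression by the MacDonald criteria counts as recurrence, and no confirmation period is required, so a lesion that clearly meets the criteria at the 12-month visit can be coded that day. This stands. A reader might infer that no lesion first suspicious at month 12 can be classified; the text does not support that. Only lesions without pathology and without clear progression stay open.

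A reader might also take the 21-22% as the proportion of primary events left uncertain. It is not: it is the share first seen at month 12, and the two coincide only if none of those lesions can be classified at the visit. The count also assumes no deaths and that all 60 lesions are evaluable. Eligibility requires only one lesion per patient of at least 1 cm, so the evaluable number may be lower.

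Nor does the point extend to lesions first suspicious at month 9. Section 5.6 allows serial MRI, DSC-PMR, PET or tissue confirmation when recurrence is suspected. Such lesions have three months of possible work-up plus a scheduled MRI inside the window.

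Finally, a 12-month horizon is reasonable for a 20-patient pilot and matches the one-year benchmark in the background, the form's comments field can hold an undetermined status, and coding rules may sit in an analysis plan that is not shown. All of this is fair. None of it supplies the later scan or pathology report, because no outcome form exists after month 12. The image archive in section 5.3, meant to allow long-term follow-up, has no later outcome form attached to it either.

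**Conclusion.** The gap is real but narrow. Sections 5.5 and 7 stop collecting outcomes at the scan on which some lesions will first look suspicious, while section 10.3 relies on later course to classify those that are equivocal and unbiopsied.

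With constant hazard, no deaths, 60 evaluable lesions and 27-33% one-year recurrence, up to about 4 of 16-20 expected events would be first seen at the last tracked MRI. That bounds the number of events left uncertain under those assumptions. Competing death lowers the share first seen then to 11-18%. Partial resolution at the visit, at an assumed quarter to a half, leaves 5-11%, or 1-2 lesions. The bound would be exceeded only if failures cluster late. The documents do not allow the unresolved fraction itself to be estimated.

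The likely damage is therefore a small number of lesions, but in an analysis with few events, and the missing information cannot be reconstructed later.

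**What to change.** Amend sections 5.5 and 7, and align section 10.3:

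- Keep month 12 as the cut-off for first suspicion.
- For any lesion suspicious but unresolved at month 12, continue the coordinators' existing audit of routine-care records for a fixed further period (for example 6 months) and record the final classification, including any pathology.
- Date a confirmed recurrence to the first suspicious MRI.
- Censor all other lesions at month 12.
- Report lesions still undetermined after the extension as such, give Appendix B an explicit entry for them, and run a sensitivity analysis coding them both ways.

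This adds no visit or scan and leaves clinical management untouched. The cost is a short amendment, a few extra chart audits, and a data lock later by the length of the extension.
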